### Moderating and process measures

#### Hot flush beliefs and behaviors

Beliefs about hot flushes and night sweats are considered moderators of the effect of the CBT program [79]. These are assessed with the Behavior Short Form HFNS Beliefs and Behavior Scale, a 16 item scale that includes items from the Hot Flush Beliefs Scale [80] and the Hot Flush Behavior Scale [81], ([name], personal communication).

#### Compliance with the intervention

Women are asked to indicate the number of CBT program modules they completed, the frequency with which they did the homework assignments and the total amount of time (in weeks) that they used the program. We are also able to monitor the actual use (frequency and duration) of the online CBT program through log data. We consider completion of the first three modules evidence of an acceptable level of program compliance because these are the modules that specifically focus on the primary outcomes.

Women who do not complete the intervention are asked to indicate their reason(s) for discontinuation (e.g., lack of motivation, illness, program burden). We assess general self-efficacy, social support and intention to complete the program as potential predictors of compliance. General self-efficacy is measured with the General Self-Efficacy scale from [82]. It includes 10 items (4 point Likert scale). Social support is assessed by the emotional/informational support subscale (8 items Cronbach’s alpha 0.96) of the Medical Outcome Study- Social Support Scale ((MOS-SS [83]). Behavioral intention is assessed by three items (5 point Likert scale) derived from the Theory of Planned Behavior [84].

#### Patients’ evaluation of the intervention program

At T1 (immediate post-intervention), women in both intervention groups are asked to complete a short questionnaire about their experience with the Internet-based CBT program. This will include questions about the perceived efficacy of and satisfaction with the program, whether they would suggest any changes to the program, and if they would recommend it to other women experiencing treatment-induced menopausal symptoms. In addition, in an effort to better understand how the program might be improved, we will conduct telephone interviews (30 min) after the T2 assessment with women who indicated on the questionnaire that the intervention did not have the desired effect and/or gave the intervention a low rating and/or would not recommend the program to others.

### Cost effectiveness

We will perform a cost-effectiveness analysis (CEA) using a validated health economic model as developed for use earlier in the EVA-trial [51]. The cost-effectiveness of the Internet-based guided CBT versus the Internet-based self-management CBT versus usual care will be expressed as: (1) cost per clinically relevant significant reduction on the problem-rating scale of the HFRS and (2) cost per QALY gained. A change of at least two points on the ten-point problem-rating scale of the HFRS, and of 0.5 SD on the FACT-ES is considered a relevant improvement [49]. A societal and hospital perspective from the Netherlands, plus a 5 year time horizon will be adopted. Future costs and effects will be discounted at 4 and 1.5%, respectively, according to the Dutch guidelines. A Markov model will be constructed with 3 mutually exclusive health states: “menopausal symptoms”, “reduction in menopausal symptoms”, and “recurrence”. Using a 6-month cycle length, the model will simulate the course of events in a hypothetical cohort of 1000 breast cancer survivors. The “effectiveness” part of the cost-effectiveness equation will be based on the HFRS (1) and SF-6D (2). The SF-6D [85], derived from the SF-36, will be mapped onto the EuroQol-5D, which will provide utilities. With the utilities, the SF-6D allows indirectly generating quality adjusted life years (QALYs) to be used in cost-effectiveness analysis.

For the direct costs, we will ask all women to report at T1 and T2 their use of health care services (e.g., GP, medical specialist, paramedical care etc.), medication use and workdays lost due to illness. In calculating the intervention costs, we will include the time spent by health professionals in providing feedback to participants (where applicable), staff training, administration, and material costs. Detailed descriptions of the intervention will be made to identify specific cost items and corresponding volumes of resource use. Subsequently, costs will be calculated by multiplying unit prices (or appropriate tariffs) by volumes of use, following the Dutch pharmacoeconomics costing guidelines [86].

The indirect costs will be measured by the Friction cost method, which is the period over which the production loss is calculated, i.e. the time that an employer needs to replace a sick employee. The calculation of the average labor costs per working day will be based on the weighted average labor costs of full-time and part-time employed persons in the Netherlands [87].

### Power calculation

The HFRS problem rating scale and the FACT-ES scale score, assessing endocrine symptoms, are the primary outcomes on which sample size calculations are based. With a total sample of 198 women (66 per group), and under the assumption of no interaction, the study will have 80% power to detect a 0.5 standard deviation difference (Cohen’s effect size) with a p value of 0.05 (two sided test) [88]. We anticipate that this effect size will be sufficient to demonstrate the efficacy of the interventions, as the CBT group intervention in the EVA-study yielded effect sizes for the primary outcomes of approximately 0.5 [44]. We will recruit 248 women into the study, to allow for an attrition rate of approximately 20% (i.e. women who discontinue participation in the study entirely, including failure to complete follow up questionnaires). Women who discontinue participation in one of the intervention groups but complete the follow up assessments will be included in the analysis.

### Statistical analysis

All data will be anonymized prior to final data analysis. The data set will not contain any personal identifiers. Only study staff will have access to these data.

Analyses will first be performed to evaluate the comparability of the intervention groups (guided versus self-management) and control group at baseline in terms of sociodemographic and clinical characteristics. ANOVA tests or appropriate non-parametric statistics will be used, depending on the level of measurement. If, despite the stratified randomization procedures, the groups are found not to be comparable on one more background variables, those variables will be employed routinely as covariates in subsequent analyses. Questionnaire scores will be calculated according to published scoring algorithms. We will compare both intervention groups with the control group over time using multilevel procedures with repeated measures, using a restricted maximum likelihood (REML) solution to model specific contrasts between groups and follow-up assessment [89]. Within each multilevel model the control group will be the reference category. For the analysis of the secondary outcome measures, appropriate statistical adjustments will be made for multiple testing. Differences in mean change scores over time between the intervention groups and the control group will be accompanied by effect sizes (ES). These effect sizes will be calculated using standard statistical procedures. Effect sizes of approximately 0.5 are considered clinically significant [90]. All analyses will be conducted on an intention to treat (ITT) basis. In addition, per-protocol (PP) analyses will be performed (as a secondary analysis) on patients who met criteria for minimal compliance with the intervention(s). Supplementary analyses will be carried out in which data relating to compliance with the program elements will be taken into account. Specifically, we will determine whether the level of compliance is associated significantly with the change over time in the primary and secondary outcomes. We will also investigate whether program effectiveness varies significantly as a function of changes in hot flush beliefs and behaviors.

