### Recruitment and randomization

We are recruiting patients from 13 community and university hospitals in the Netherlands. We identify potentially eligible patients through hospital registries and the database of the Netherlands Cancer Registry. Potentially eligible patients are sent a personalized letter by their treating physician informing them about the study and the Internet-based program. Women are asked to respond to this invitation by returning either a short screening questionnaire (when there is interest in participating), or a postcard indicating reasons for declining participation. Non-respondents are sent a reminder 2 weeks after the first invitation.

The women who express interest in the study, but do not meet the eligibility criteria receive a personalized letter that explains why they are not eligible. When initial eligibility criteria are met, women are contacted by telephone to confirm their eligibility, to explain the Internet-based program and the RCT, and to confirm their willingness to invest the requisite time and effort if they are randomized to either of the two intervention groups. A baseline questionnaire and informed consent form are sent to eligible and motivated patients. Upon return of both to the study staff, patients are randomized to the guided Internet-based CBT group (*n* = 83) the self-management Internet-based CBT group (*n* = 83) or to a usual care, ‘waiting-list’ control group (*n* = 82) using the minimization technique [70] with age (<40 years; 40–45 years, >45 years), current endocrine treatment for breast cancer (yes; no), time since chemotherapy (<1 year; 1–3 years; > 3 years) and current use of non-hormonal treatments for hot flushes (antidepressants, clonidine, gabapentin) (yes; no) as stratification variables. Due to the nature of the study, blinding is not possible.

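### Baseline tests between randomised groups choose the covariates for every later model; the rule follows chance and in practice passes over the four minimisation factors

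*Protocol article*

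**What the plan says.** The Statistical analysis section of the protocol article begins with a comparison of the three groups on sociodemographic and clinical characteristics, using ANOVA or non-parametric tests. If, despite stratified randomisation, "the groups are found not to be comparable on one more background variables, those variables will be employed routinely as covariates in subsequent analyses". This is the only covariate rule in the article. No significance level and no closed list of variables accompany it.

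The primary analysis is a REML multilevel model with repeated measures and the control group as reference. Results are reported as differences in mean change over time. None of the model's covariates is named.

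Under Recruitment and randomization, women are allocated "using the minimization technique [70] with age (<40 years; 40–45 years, >45 years), current endocrine treatment for breast cancer (yes; no"), together with "time since chemotherapy (<1 year; 1–3 years; > 3 years) and current use of non-hormonal treatments for hot flushes". The same section says that blinding is not possible.

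**The concern.** The groups are formed by a random procedure, so a significant baseline difference is a chance event. Its p-value measures how unusual the imbalance is and says nothing about whether the variable predicts the hot flush problem rating or the FACT-ES score. A rule built on it admits variables that may be irrelevant and leaves out prognostic ones that happen to be balanced. The primary model is then unknown until the baseline data have been examined by arm.

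The rule also runs against the design. Minimisation forces balance on four factors, presumably chosen because they were thought to matter. Balanced factors do not fail a baseline test, so the rule passes over them. Yet an analysis after minimisation should condition on these factors if its standard errors are to reflect the balance obtained. What is at stake is a fixed primary model and some precision, not protection against false positives.

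**Working it through.** **1. The plan's own figures.** The Power calculation section gives "With a total sample of 198 women (66 per group"), says "the study will have 80% power to detect a 0.5 standard deviation difference" "with a p value of 0.05 (two sided test"), and adds "We will recruit 248 women into the study, to allow for an attrition rate of approximately 20"%.
- Expected z = 0.5 × √(66/2) = 2.872. Power = Φ(2.872 − 1.960) = 0.819 (0.814 by noncentral t).
- 198 / 0.80 = 247.5, rounded up to 248.

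Both reproduce. Nothing below changes the sample size.

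**2. How often chance triggers the rule.** P(at least one flag) = 1 − 0.95^k, assuming k independent variables and a 5% level.

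| k | P(at least one flag) |
|---|---|
| 8 | 34% |
| 10 | 40% |
| 12 | 46% |
| 15 | 54% |

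The section on sociodemographic and clinical data lists about 13 variables. Age, medication use and treatment history overlap the minimisation factors, which leaves about 10. A simulation with 10 variables gave 40–41%.

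**3. Whether the rule ever selects the minimisation factors.** Three-arm minimisation of 198 women on four factors was simulated with assumed prevalences. In 1,000 allocations × 4 factors = 4,000 baseline tests, none reached p < 0.05. The result was the same when allocation followed the minimising arm with probability 0.8 and was otherwise random.

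**4. Cost of omission, single follow-up comparison.** If the factors explain a share R² of outcome variance and are fully balanced, the unadjusted SE is too wide by 1/√(1 − R²), and type I error is 2Φ(−1.96/√(1 − R²)).
- R² 0.10: 1/√0.90 = 1.054; type I error 0.039.
- R² 0.20: 1/√0.80 = 1.118; type I error 0.028.

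Simulation (d = 0.5, 66 per group, 2,500 runs per row, strict minimisation):

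| Assumed R² | SE relative to true SD, factors omitted | Type I error, omitted / included | Power, omitted / included |
|---|---|---|---|
| 0.05 | 1.02 | 0.043 / 0.050 | 0.83 / 0.84 |
| 0.10 | 1.06 | 0.036 / 0.046 | 0.82 / 0.85 |
| 0.20 | 1.12 | 0.032 / 0.055 | 0.83 / 0.90 |
| 0.30 | 1.17 | 0.021 / 0.052 | 0.84 / 0.92 |

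**5. Cost of omission, repeated-measures change model.** Assumed variances: factor 0.2 (R² 0.20, constant over time), between-woman 0.4, residual 0.4.
- T0 as an outcome, group-by-time contrast: the factor cancels. SE ≈ √(4 × 0.4/66) = 0.156. The fitted models gave 0.1563 without the factor and 0.1563 with it.
- Baseline means constrained equal: the within-woman correlation is 0.6 without the factor and 0.4/0.8 = 0.5 with it. The residual variance given baseline is 1 × (1 − 0.36) = 0.64 against 0.8 × (1 − 0.25) = 0.60, and √(0.64/0.60) = 1.033. The fitted models gave 0.1400 without and 0.1356 with the factor, about 3% wider without it.

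**6. Selection by baseline test.** With 10 candidate variables over 4,000 runs, type I error stayed at 0.043–0.051. With 10 prognostic covariates and R² 0.20, power was 0.82, against 0.87 for prespecified adjustment.

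**The case against.** The strongest reply is that this is a condensed article and the full protocol and analysis plan are not shown. Those documents commonly name the design factors as model terms, and no sentence in the article excludes them. This stands: a reader might infer that the four factors are definitely left out, and the text does not support that. It supports only that the stated rule will not bring them in and that no other route is given. The rule itself is stated outright, so it is not a missing detail.

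A reader might also infer that the standard errors are too wide as a matter of fact. That does not follow. The article gives no R² for the factors. The 6% to 12% belongs to a single follow-up comparison, whereas the article describes change over time with T0 measured before randomisation. If T0 is an outcome in that model, time-constant effects cancel and the loss can be nil.

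Nor is false-positive risk raised or the trial underpowered. Omission is conservative, selection by baseline test left type I error near 0.05, and simulated power without the factors (0.82–0.84 for R² from 0.05 to 0.30) stays above the planned 80%. The loss is measured against a better analysis, not against the plan.

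Finally, counting all 13 listed variables gives 1 − 0.95^13 = 49%. That includes variables overlapping the minimisation factors, which are almost never flagged, so about 40% is the fairer figure. Even that is approximate, because weight and height, or marital status and living situation, are not independent.

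**Conclusion.** The covariate rule is a poor one and should be withdrawn. It makes the primary model depend on chance imbalance, with about a 40% probability of at least one flag (10 independent variables, 5% level, both assumed), and in practice it never selects the four minimisation factors.

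The effect on precision is conditional. It requires that the factors predict outcome, and it depends on a model form that the article leaves open: about 6% to 12% at R² 0.10 to 0.20 for a single follow-up comparison, nil to about 3% at R² 0.20 for a change model. Any error is in the conservative direction. The point is a worthwhile, inexpensive correction and does not threaten the trial's validity.

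**What to change.** - Delete the sentence that turns baseline differences into covariates, and present the baseline table descriptively without tests.
- Prespecify the four minimisation factors and the baseline score of the outcome as covariates in all primary and secondary models, with the T1 and T2 scores as the outcome.
- If T0 is kept as an outcome, add factor-by-time terms. Main effects alone leave the group-by-time contrast essentially unchanged (step 5).
- Give time since chemotherapy a level for women who had none. The Study sample section admits menopause induced by hormonal therapy or oophorectomy alone, and the three printed levels have no place for these women; without such a level they could drop out of the model and so out of the intention-to-treat analysis.

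The cost is a few sentences, one coding decision and a few degrees of freedom: 2 + 1 + 2 + 1 = 6 for the factors as printed, one more for the added level and one for the baseline score, among 198 women. The factors and baseline scores are already collected, and the sample size does not change.

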Several limitations of the trial should also be noted. First, it would be valuable to compare the Internet-based CBT groups with a face-to-face CBT group in order to compare compliance, experience and effectiveness. However, recruitment and follow up proved to be problematic in our previous group CBT trial (EVA-study) [44]. Also we consider it important to first establish the efficacy of the Internet-based CBT program. Second, we anticipate that both intervention groups (guided and self-management) will be effective, in comparison with the control group. The trial was powered based on the estimated effects of each of the two Internet-based CBT interventions in comparison to the control group. It may also be the case that one of the two CBT programs is more or less effective than the other. One would hope, given the additional costs involved, that the guided CBT program would be more efficacious than the self-management CBT program. However, if such differences exist, the magnitude of difference will likely be smaller than that expected between the CBT programs and the control group. In order to detect a smaller difference (effect size) when comparing the two variants of the CBT program, we would need a substantially larger sample size [88]. Unfortunately, our budget, both in terms of financial resources and time, does not allow us to increase the sample size. Nevertheless, within the limits of statistical power available to us, we will calculate between CBT group differences in both efficacy and cost-effectiveness outcomes. Finally, although women in the waiting-list control group will not be provided with any materials or program elements, they might look for other options themselves. However, we do not anticipate that this will take place in a structured or systematic way. In any case, at each assessment point, women are asked to report any activities that they may have undertaken to alleviate their menopausal symptoms.

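### The treatment effect is described as a difference in mean change and no baseline outcome adjustment is named; using T0 in the REML model would gain precision at no cost, although the stated 80% power is not shown to be wrong

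*Protocol article*

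**What the plan says.** **Model and effect measure** (Protocol article, Statistical analysis). Both CBT arms are compared with control over time in a multilevel repeated-measures model fitted by REML, with control as the reference category. The effect is then described as follows: "Differences in mean change scores over time between the intervention groups and the control group will be accompanied by effect sizes (ES").

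**Covariates** (same section). Groups are first checked at baseline on sociodemographic and clinical characteristics. Background variables found not comparable become covariates. The baseline score of the outcome is not mentioned in this rule, and it is not one of the minimisation factors listed under Recruitment and randomization.

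**Timing of T0** (Data collection). The baseline questionnaire is completed before randomisation. Follow-up is at 10 weeks (T1) and 6 months (T2).

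**Sample size** (Power calculation). The section takes 66 analysable women in each of the three arms, 198 in all, and a two-sided alpha of 0.05. On that basis it claims that "the study will have 80% power to detect a 0.5 standard deviation difference (Cohen’s effect size"). One condition is attached to this claim: "under the assumption of no interaction". For the size of the effect it relies on an earlier trial: "the CBT group intervention in the EVA-study yielded effect sizes for the primary outcomes of approximately 0.5". The section does not say whether the SD is that of the raw score or of the change, and it gives no correlation. The Discussion confirms which comparison is powered: "The trial was powered based on the estimated effects of each of the two Internet-based CBT interventions in comparison to the control group".

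**The concern.** T0 precedes randomisation, so the true T0 means of the three arms are equal by design. A model that estimates a separate T0 mean for each arm ignores this. With complete data, its group-by-time contrast is then the plain difference in mean change. That estimate is unbiased, but it carries the full sampling noise of the T0 difference between arms.

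The text does not settle how T0 enters the model. However, the two things it does state, an effect expressed as change and a covariate rule driven by observed imbalance in background variables, both point to the unadjusted contrast. At stake is the precision of every arm-versus-control estimate on both primary outcomes (HFRS problem rating and FACT-ES) and on the secondary questionnaire scores measured at T0.

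**Working it through.** **Inputs.** 66 analysable women per arm, difference 0.5 SD, two-sided alpha 0.05 (Power calculation). The correlation r between T0 and follow-up is not in the document. It is assumed here over 0.3 to 0.8.

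**1. The plan's own figure.** For a simple comparison of two means with SD 1:
- n per arm = 2(1.96 + 0.84)²/0.5² ≈ 63, or 64 with the t distribution. The plan has 66.
- Power at 66 per arm: 0.5 × √(66/2) = 2.87, and Φ(2.87 − 1.96) = 81.9% (81.4% with the t distribution).
- Recruitment: 198/(1 − 0.20) = 247.5, rounded up to 248, as stated.

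The stated 80% reproduces.

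**2. Variance of the two contrasts.** Take equal SDs at T0 and follow-up, in units of the raw-score SD, at one follow-up time:
- difference in change: 2(1 − r)
- baseline-adjusted difference: 1 − r²
- ratio: 2(1 − r)/(1 − r²) = 2/(1 + r), which exceeds 1 for every r below 1.

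**3. Numbers.** The power columns use 66 per arm and the normal approximation, and they treat 0.5 as raw-score SD units.

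| r (assumed) | Var., change | Var., adjusted | Ratio | Power, change | Power, adjusted |
|---|---|---|---|---|---|
| 0.3 | 1.40 | 0.91 | 1.54 | 68.0% | 85.3% |
| 0.4 | 1.20 | 0.84 | 1.43 | 74.6% | 88.0% |
| 0.5 | 1.00 | 0.75 | 1.33 | 81.9% | 91.3% |
| 0.6 | 0.80 | 0.64 | 1.25 | 89.5% | 94.8% |
| 0.7 | 0.60 | 0.51 | 1.18 | 96.0% | 98.0% |
| 0.8 | 0.40 | 0.36 | 1.11 | 99.5% | 99.8% |

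In confidence-interval width, the change contrast is wider by √1.54 = 1.24 at r = 0.3, √1.33 = 1.15 at r = 0.5 and √1.18 = 1.09 at r = 0.7.

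**4. Where the change contrast reaches 80%.** In raw-score SD units this happens at r of about 0.475: variance 2 × 0.525 = 1.05, and 2.87/√1.05 = 2.80, which gives Φ(0.84) ≈ 80%. If the 0.5 is instead in units of the SD of change, power for the change contrast is 81.9% at every r. The adjusted contrast would then do better by the same variance ratio.

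**5. Two follow-ups.** If T1 and T2 were averaged, with the same correlation r between all time points:
- change variance: (1 + r)/2 + 1 − 2r = 1.5(1 − r)
- adjusted variance: (1 + r)/2 − r² = (1 − r)(1 + 2r)/2
- ratio: 3/(1 + 2r), which is 1.88 at r = 0.3 and 1.50 at r = 0.5.

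Averaging raises power for both contrasts (the change contrast reaches about 80% at r = 0.3), but it does not remove the loss. The article defines no pooled contrast.

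**The case against.** **The model may already adjust.** The quoted sentence says which quantity receives an effect size. It does not specify the estimator. A REML model with T0 means constrained equal is also a repeated-measures multilevel model and also yields differences in mean change. A condensed article may leave this detail to the full protocol or analysis plan. This stands: the text does not rule out adjustment. What remains is that the effect measure and covariate rule it does state lead towards the unadjusted contrast, and naming the better model costs nothing.

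**It is a preference, not an error.** Also true. Under randomisation the change contrast is unbiased, and the point is about efficiency only.

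**Stronger readings that a reader might infer, and that the document does not support:**
- *That the trial misses its stated 80% power.* This needs two inputs the document does not give: 0.5 in raw-score SD units, and r below about 0.475. The nearest figure, the HFRS test-retest reliability of 0.80 in Table 2, is not a 10-week or 6-month correlation, but it gives no support for a low r.
- *That* "under the assumption of no interaction" *contradicts the group-by-time effect being tested.* The article does not say which interaction is meant. It may mean an effect that is constant over follow-up.
- *That the entry criterion lowers r and so lowers power.* Eligibility requires a mean of 2 or higher on a 0–10 problem rating and does not select on FACT-ES. With follow-up-on-baseline slope b, the change variance is (1 − b)² × var(T0) + residual. It falls when var(T0) is narrowed, so a lower r does not by itself mean lower power for a given absolute effect. The same expression shows that the adjusted contrast, which keeps only the residual, is not less precise in large samples even without equal variances.

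**Conclusion.** The point holds as a free improvement. If T0 is a free outcome, as the wording suggests but does not fix, the arm-versus-control contrasts carry 1.54, 1.33 or 1.18 times the necessary variance at r = 0.3, 0.5 or 0.7. These ratios assume equal SDs at T0 and follow-up, complete data, one follow-up time and an r that the document does not supply. The direction of the loss holds at every r below 1.

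The sample size is sound on its own inputs, and a power shortfall is not established. What the Power calculation lacks is the SD to which the 0.5 refers, and this decides whether r affects the power of a change contrast at all.

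**What to change.** **In Statistical analysis**, state how T0 enters the REML model, in one of two ways:
- keep T0, T1 and T2 as outcomes and constrain the T0 means to be equal across the three arms; or
- model T1 and T2 as outcomes, with the T0 score of the same outcome as a covariate, included whatever the observed imbalance.

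Report the adjusted mean difference from control at T1 and at T2, and name the SD used to turn it into an effect size. With a common T0 mean, this difference is also the difference in mean change, so the planned form of reporting can stay.

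**In Power calculation**, say whether 0.5 refers to the SD of the raw score or of the change, and which interaction is assumed absent. If it is the raw-score SD, add the assumed correlation and the resulting power.

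**Cost.** Wording and model specification only. T0 scores are already collected from every woman before randomisation, so no patients, visits or data are added.
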